## Background

### Medical decision making and the important role of communication

Good clinical practice is characterized by valuable interactions between an informed and activated patient and a proficient, proactive health care team [1]. Such interactions require a patient-health provider communication that is patient-centered, and responsive to patient needs, values, and preferences [2]. Effective communication has been associated with improvement in medical and psychological outcomes, greater patient confidence in and adherence to treatment plans, increased care satisfaction, and improved trust in health care providers [3]. Moreover, thorough patient information is an ethical obligation for the care provider [2,4]. For decisions about diagnostic or treatment options, a shared decision-making (SDM) process, where physicians and patients exchange information and perspectives is increasingly regarded as the ideal model [5]. SDM is characterized by a discussion of different options and outcomes and by the fact that patient and physician arrive at a consensus. To have unbiased and understandable information about options evidence-based patient information has been considered a prerequisite of SDM [6].

SDM is particularly suited to medical situations meeting the equipoise condition - when none of the available options appears clearly superior for an individual patient [7]. The equipoise condition is especially relevant to decisions regarding chronic illnesses with uncertain prognoses and for which treatments are only partially effective, or associated with important side-effects.

One of the most cited goals of SDM is to support medical decisions that are informed and coherent with patients' values [8]. However, the mediating principle by which SDM is hypothesized to achieve this goal has not yet been described. The method itself remains insufficiently operationalized [9,10].

### Measuring involvement

There are few instruments designed to measure SDM in clinical practice. One of the instruments most frequently used is the Observing Patient Involvement (OPTION) scale, in which an independent observer measures the extent to which clinicians initiate behavior to involve patients during the consultation [11]. This measurement strategy isn't sufficient to study clinical decision-making in its dyadic and relationship-centered approach. It is crucial to assess simultaneously patient and clinician behavior, and looking at the interaction by analysis of the fitting of communicative styles between a given patient and his physician [10,12,13]. It has been shown judging medical communication from different perspectives (physicians, patients and external observers) leads to discrepant results [14-17], and none of the existing measurement approaches can be regarded as a gold standard to assess the degree of sharing in the decision-making dyad [12,18,19]. Although the OPTION scale has provided valuable data about decision-making processes, it is only able to represent external assessments; the perceptions of participants involved in the consultation remain unavailable [20]. Based on reviews of SDM assessment instruments [12,19] a new tool, the "Multifocal approach to the sharing in SDM" (MAPPIN' SDM) has recently been developed in Hamburg (see below for details).

### The role of uncertainty in processing a medical decision and methodological implications

The decision-making process in the clinical encounter is influenced by its inherent uncertainty and by the reaction of physicians and patients to this uncertainty. Uncertainty is a feature of many aspects of physician-patient risk communication. Uncertainty is inherent in the individual prognosis and in the capacity of a treatment to improve the patient's health. Uncertainty is inherent in assessment of the physician's competence as well as in the assessment of the patient's understanding of given explanations. Uncertainty is also inherent in the interpretation of statistics, especially when evidence is lacking. Most of the uncertainties cannot be resolved within a conversation but nevertheless have to be managed. Abstracting from the particular decision, for instance on a prostate cancer screening or treatment for relapses of multiple sclerosis, we define uncertainty as the core content of the decisional communication. Uncertainty is referred to in some of the SDM literature [7,21,22]. For instance, reducing awareness of uncertainty is seen as an important goal of risk communication by some authors [23]. Given the context of uncertainty, decisional conflict is one of the key elements in decision making in clinical settings [24]. "Decisional conflict is defined as an individual perception of uncertainty about which course of action to take when choice among competing options involves risk, loss, regret, or challenge to personal life values. In lay terms, decisional conflict refers to the level of comfort that an individual experiences when facing a difficult decision. Decisional conflict should not be confused with the uncertainty inherent in the nature of the available scientific evidence. Until recently, decisional conflict in patients as well as in physicians had been studied at the level of the individual rather than at the level of the dyad, thus ignoring the interpersonal system that is at play. Individuals involved in dyadic interactions, even brief ones, can, and often do, influence each other's cognitions, emotions, and behaviours" [25]. Beyond this more quantitative approach to perception of uncertainty the methodological concept of SDM has to specify a strategy to communicate uncertainty [26]. Such a strategy might mean support for a patient, since awareness of various uncertain aspects in a decision prevents the patient from achieving a position of clarity. Negotiation of uncertainties in the medical encounter should lead to changes in the patient's cognitive representation of uncertain aspects. Beyond increasing or reducing uncertainty in the perception of the person concerned, such negotiation can change the state of the cognitive representation. There is a need for a theory about people's perception of decisional uncertainty and about the way it changes when they elaborate information relevant for this decision [27].

## Objectives

1. To evaluate a new intervention's ability to enhance physicians' communication behavior and to improve the communication in terms of SDM.

2. To further validate a newly deduced coefficient expressing the degree to which a communication involved physician and patient in an evidence-based decision making process as the gold standard for measuring SDM.

3. To evaluate SDM regarding its effects on patients' decisional conflict and internal processes of elaboration.

### Sub goals

- To further validate the short version of the Uncertainty Profile questionnaire (UP24) which is supposed to assess an individual's perception of uncertain aspects when facing a decision.

- To yield data on the interrelatedness of different perspectives on communication.

The project builds up on own previous studies and is structured to address all three study questions within one clinical trial.

## Methods

### Trial Design

This is a multi-center randomized controlled trial comparing a group of physicians which receives training with a waiting control group regarding the SDM performance of the doctor-patient-dyad. Within the total pool of consultations, in both groups the impact of the actual communication level according to SDM on indicators of thorough elaboration of the decision will be investigated (see Figure 1).

**Figure 1 F1:**
[figure not shown]
**Flow of randomly assigned participants in the two experimental conditions**.

### Participants

As the study sample medical consultations between physicians and patients will be monitored in seven university outpatient clinics in Germany (oncology, gynecology, psychiatry, neurology, dentistry, radiology). Consultations are eligible if the physician expects a medical decision to be negotiated within the encounter. Patients are included in the study only one time, while physicians document a sequence of four consultations each.

### Intervention

The intervention is a training curriculum (doktormitSDM [28]) addressing the doctors and goaling (intending) at stimulating efforts to involve their patients in the decision making process. It has been developed based on the newest available scientific knowledge on evidence-based patient information (EBPI) and SDM [29,30]. Its didactic is inspired by training techniques from psychotherapy education and enables the participants to incorporate the theoretical framework of reference in their cognitive system by use of examples drawn from own communication behavior. Therefore, the training both coaches the physicians as observers of communication and provides feedback to them.

In particular, the training includes 3 educational components:

*i1. The manual: *It was developed to comprehensively explain background and idea of SDM as well as a set of 15 SDM skills which represent an extension of the range of skills published by Elwyn et al. [11,31]. Within the manual examples are used to illustrate varying degrees of performance.

*i2. The training video: *Corresponding with the manual a training video was developed and produced. It demonstrates excellent performance of each of the 15 indicators applied to a decision on immunotherapy in multiple sclerosis. The video shows a neurologist talking to a patient. The consultation is role play based on a prepared script. Within the video, each skill is verbally edited according to the MAPPIN'SDM framework.

*i3. The face to face feedback: *Trainees get structured feedback based on an assessment of a video-recorded own consultation in terms of the same framework of reference. The feedback session lasts a maximum of 15 minutes and follows a guideline passing 6 separate steps:

1. intro via surveying subjective benefit of the previous training steps

2. statement that feedback does not refer to communication performance in general, but just to our specific viewpoint. The trainer indicates, that there are a lot of other important aspects of communication, one could focus on. The present focus is the way the physician involves the patient into the decision to be made.

3. actualization of the specific consultation. Reporting context or particular events. e.g. by presenting a sequence of the video. Noting subject of the decision and duration of the decision sequence

4. concrete positive feedback referring to observable skills supported by presentation of video sequences.

5. investigation of the doctor's ideas regarding potential for improvement

6. suggestions regarding potential improvement. Concrete examples are provided which as far as possible build up on existing competencies. Checking understanding. Reassuring tolerable volume of input.

The training deliberately abandons to provide the trainees with a general judgment of their performance, or to reach completeness in the feedback of the communication skills. Furthermore, the feedback is not intended to go beyond the concrete consultation for instance by relating it to other consultations. The feedback aims at concreteness and traceability.

### Outcomes

As it is considered important that the trial does not negatively affect the practice process by burdening physicians and patients too much, measurement is limited to the necessary amount of instruments. Most of the measures were tested in previous studies to explore item properties and validity. In particular measures were selected to assess:

a. both parties' mutual involvement in the decision making process using the MAPPIN'SDM inventory (objective judgment based on video-tapes, physician and patient questionnaires (15 items each))

b. the patients' perception of SDM using the SDM-Q (9 items)

c. to which extent involvement (in terms of SDM) impacts on the dyadic perception of decisional conflict using the Decisional Conflict scale (16 items to be administered by physicians and patients)

d. patients' cognitive representation of decision related uncertainty using the UP24 (24 items to be administered by the patient before and after the consultation).

#### Measuring involvement by use of the MAPPIN'SDM approach

MAPPIN'SDM [32] is a measurement system comprising 7 coherent views on SDM: I) SDM related behavior shown by 1) patient, 2) doctor, 3) the doctor-patient-dyad, judged by an independent observer on the basis of video documents; II) the doctor's perception of 4) the dyad's SDM related behavior and 5) its perceived result; III) the patient's perception of 6) the dyad's SDM related behavior and 7) its perceived result. Each focus is assessed by the identical set of 15 criteria with slightly adapted formulations. This set incorporates all items of the OPTION scale [11,31] plus 4 indicators considered essential in the SDM literature.

While the complete system with 7 foci was initially developed to consequently map every possible view on SDM and thereby their interrelatedness [32], SDM can be sufficiently defined by a combination of 3 noteworthy parts. We call a decision making process "shared" if a) SDM behavior is shown by the doctor-patient-dyad (focus 3), b) the patient gets the impression of being involved (focus 7), and c) doctor and patient *share* this impression (concordance between foci 7 and 5). The formula below shows how the 3 parts are adjusted and combined to a compound measure called SDM_MASS _(SDMmeeting its concept's assumptions). SDM_MASS _ranges from 0 to 1, where 0 indicates no SDM and 1 indicates perfect SDM.

$${\text{SDM}}_{\text{MASS}}=\frac{\frac{\text{M(MAPPIN}-{\text{Qp}}_{\text{patient}})}{4}+\frac{\text{M(MAPPIN}-{\text{O}}_{\text{dyad}})}{4}+\tau_{1-15}(\text{MAPPIN}-{\text{Q}}_{\text{patient}};\text{MAPPIN}-{\text{Q}}_{\text{doctor}})}{3}$$

MAPPIN - Q_patient_: Patient questionnaire addressing his/her perceived result of SDM

MAPPIN - O_dyad_: Observer rating addressing the realized amount of SDM on the dyadic level

MAPPIN - Q_doctor_: Physician questionnaire addressing his/her perceived result of SDM

M: Mean of items of the particular domain (range 0-4)

τ_1-15_: Kendall's tau coefficient indicating consensus (concordance) on items 1-15; negative values are fixed at 0.

SDM_MASS _serves as primary endpoint for the evaluation of the training (study question 1). Accordingly, in the present study each consultation is measured using the three observer foci (MAPPIN-O_doctor _, MAPPIN-O_patient _, MAPPIN-O_dyad_) based on video data. Observation based analyses (3 × 15 items = 45 items per consultation) will be conducted by two independently working trained MAPPIN'SDM raters with previously proven inter-rater-agreement. Doctors and patients each judge the perceived SDM result by use of the MAPPIN-Q_patient _/MAPPIN-Q_doctor _after the consultation. Before filling in the questionnaires both parties shall cooperatively define the specific medical decision they will refer to. Completing these questionnaires requires about 5 minutes.

In addition, OPTION scores will be extracted from the observer data. OPTION serves as secondary endpoint of study question 1 and is used to validate MAPPIN-O_dyad _(study question 2).

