### Sample Size

The calculation of the required sample size is primarily oriented towards the demands of study question 1 which addresses the evaluation of the training.

We aim at a power of 85%. Given an effect size of d = .9 (which was already realized with a former version of the training), a one-tailed t-test for two independent samples with an alpha of .05, a total sample size of N = 36 is needed. In order to take possible drop-outs into account, the sample size is expanded to N = 40.

Regarding study question 2 (validation of the components of SDM_MASS_), a number of N = 36 physicians (minimum after possible drop-outs) leads to 4 × 36 = 144 consultations in the whole study. Given alpha = .05, power = .85, this sample size would require correlations of .22 between the components of SDM_MASS _and the external criteria OPTION and DCS_concordance_. For the validation of the patient component by use of SDM-Q, only N = 76 consultations are available since the remaining complete the UP24 instead. This demands a correlation of at least .30 to yield significant results. Both these values are far below our expectations.

Regarding study question 3, correlation between SDM_MASS _and DCS_patient _has to exceed .22 (N = 144). Correlation between SDM_MASS _and ΔELAB has to go beyond .31 (N = 68). Both is regarded as achievable.

Summing up, determining sample size according to study question 1 leads to sufficient power regarding the remaining study questions.

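### OPTION is not an external criterion for MAPPIN-O_dyad: it comes from the same ratings, so a significant correlation is weak evidence for the observer component of SDM_MASS

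*Protocol article*

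**What the plan says.** In the protocol article, the section on the MAPPIN'SDM approach describes three observer foci (doctor, patient, dyad), each rated from video. Of the criteria it says: "Each focus is assessed by the identical set of 15 criteria with slightly adapted formulations". Of their content: "This set incorporates all items of the OPTION scale [11,31] plus 4 indicators considered essential in the SDM literature". The ratings "will be conducted by two independently working trained MAPPIN'SDM raters with previously proven inter-rater-agreement", giving 3 × 15 = 45 items per consultation.

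No separate OPTION rating is planned: "OPTION scores will be extracted from the observer data". The next sentence gives OPTION two roles: "OPTION serves as secondary endpoint of study question 1 and is used to validate" MAPPIN-O_dyad, which belongs to study question 2. The article does not say which of the three foci supplies the OPTION score. The Background section Measuring involvement describes OPTION as an instrument in which "an independent observer measures the extent to which clinicians initiate behavior to involve patients during the consultation", which points towards the doctor focus but does not settle it.

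Sample Size lists "the external criteria OPTION" and DCS concordance as the yardsticks for the components of SDM_MASS, with a required correlation of .22 at N = 144, alpha .05 and power .85. For the patient component, checked against SDM-Q at N = 76, it says: "This demands a correlation of at least .30 to yield significant results". For study question 3 it gives .22 (N = 144) and .31 (N = 68). Statistical Methods names Spearman correlation for convergent validity. Objectives and Discussion present SDM_MASS as the intended gold standard.

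**The concern.** A validation criterion is informative to the extent that its errors and content are separate from those of the measure under test. Here the criterion is a rescoring of the instrument's own ratings. Agreement between the two then mixes three things: real agreement about the consultation, identical item content, and errors or impressions that one rater carries from item to item. A test against zero correlation cannot tell them apart.

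At stake is the observer part of study question 2. MAPPIN-O_dyad is one of the three terms of SDM_MASS, and a significant correlation with OPTION would be read as external support for it.

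A second, smaller matter is how Sample Size describes its correlations. It presents a power figure as the size that an observed correlation must reach to be significant.

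**Working it through.** **Inputs from the article.** MAPPIN criteria per focus: 15. Non-OPTION criteria: 4. Shared criteria: 15 − 4 = 11. Consultations: 144 for OPTION and DCS, 76 for SDM-Q, 68 for ΔELAB. Alpha .05, power .85. Sidedness is stated (one-tailed) for study question 1 only.

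**1. The article's own figures.** Detectable correlation by Fisher's z: r = tanh[(1.645 + 1.036)/√(N − 3)], one-sided, null correlation 0. Critical observed correlation: r = t/√(N − 2 + t²), with t the 95th percentile on N − 2 degrees of freedom.

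| N | Stated | Detectable, one-sided: Fisher z / noncentral t | Detectable, two-sided: Fisher z / noncentral t | Observed r needed for significance: one-sided / two-sided |
|---|---|---|---|---|
| 144 | .22 | .222 / .219 | .247 / .244 | .138 / .164 |
| 76 | .30 | .304 / .297 | .337 / .329 | .190 / .226 |
| 68 | .31 | .321 / .312 | .355 / .346 | .201 / .239 |

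The stated values are correctly calculated as one-sided detectable correlations with 85% power. They are not significance thresholds: at N = 76 an observed .19 is already significant one-sided, and .23 two-sided.

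**2. OPTION taken from the dyad ratings.** The 11-item mean is then part of the 15-item mean. For items of equal variance with common inter-item correlation ρ:

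r = √{ 11(1 + 14ρ) / [15(1 + 10ρ)] }

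- ρ = 0: √(11/15) = .856
- ρ = .1: √(26.4/30) = .938
- ρ = .3: √(57.2/60) = .976

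As a check, 5,000 trials of 144 consultations were simulated with purely random 0–4 item scores. The mean Spearman correlation was .84, the minimum .74, and all were significant.

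**3. OPTION taken from the doctor-focus ratings.** No item score is then shared, so the result depends on quantities the article does not give. Two illustrations, both resting on assumed values:

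- If the same criterion correlates q between doctor and dyad foci, and different criteria are uncorrelated, the scale correlation is q × √(11/15). For q from .5 to .9 this is .43 to .77. Part of q may be genuine, because a doctor who involves the patient also raises the dyad's performance.
- If there is no true association, but a common rater or video impression takes up a share h of item variance, 2,000 simulated trials per value gave significance in 4.7% (h = 0), 77% (h = .02) and 100% (h = .05) of trials. The mean correlations were 0, .20 and .38.

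**4. Whether crossing the raters is enough.** Correlating one rater's full dyad score with the other's OPTION score removes shared rater error but keeps the 11 shared criteria. With otherwise uncorrelated items, a same-item correlation between raters of q = .52 still gives .52 × .856 = .445. The item overlap has to be removed as well.

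**The case against.** The strongest reply is that the article does not say OPTION comes from the dyad ratings. OPTION measures clinician behaviour, the doctor focus is scored separately, and on that reading the correlation can come out null: with no shared rater or video variance the simulated rejection rate is the nominal 5%. This stands. A reader might infer that the validation cannot fail; that holds only under the dyad-focus reading. The doctor-focus figures rest on assumed values and cannot be used to say how large the inflation is.

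It is also fair that OPTION bears on one component only. SDM-Q and DCS concordance are separate instruments, and the article speaks of further validation after earlier studies. A reader might infer that the whole gold-standard aim rests on a circular check; the article does not support that.

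Three further inferences should be resisted:

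- The absence of a minimum acceptable correlation is not an error. A floor such as .30 would be a reviewer's choice, and a condensed article may leave it to the full protocol or analysis plan.
- The .22 is not miscalculated, and its sentence does state the power.
- One could say that a pass mark of .22 or .30 would be met only half the time when the true correlation equals it. Nothing in the article applies those values as pass marks for validity.

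The reply does not rescue the word external. Under either reading, the same rater team scores both measures from the same videos on the same criteria.

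**Conclusion.** The point holds in limited form. Calling OPTION external conflicts with the article's own account of where the score comes from. Under the dyad-focus reading the correlation is at least about .86 for equal-variance, non-negatively correlated items, and significance against zero is assured. Under the doctor-focus reading it is inflated by an amount that the article gives no means of fixing. Either way, a significant result is weak evidence for MAPPIN-O_dyad. The other two components of SDM_MASS and the training comparison on SDM_MASS in study question 1 are not touched by this.

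The description of .30 as the correlation needed for significance at N = 76 is wrong; the figure itself is right as a one-sided detectable correlation. The .22 and .31 for study question 3 are likewise worded as values to be exceeded, although .14 (N = 144) and .20 (N = 68) would be significant one-sided.

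The item count of 11 is the article's own, by subtraction.

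**What to change.** 1. State which observer focus supplies the OPTION score, and stop describing OPTION as external.
2. As the validity analysis, correlate one rater's OPTION score with the other rater's mean of the four non-OPTION MAPPIN-O_dyad items, repeat with the raters exchanged, and average the two. This needs both raters to score every video, which the article implies but does not state.
3. Report the estimate with a confidence interval that allows for four consultations per physician, for example by resampling physicians. A minimum value may be set in advance if the sponsor wishes; it is optional.
4. Keep the full-scale correlation of MAPPIN-O_dyad with OPTION, but label it internal consistency.
5. In Sample Size, describe .22, .30 and .31 as correlations detectable with 85% power at one-sided alpha .05, and delete the statement that .30 is required for significance.

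The cost is wording and one reanalysis of ratings already planned. A four-item score from a single rater is less reliable, so the correlation will be lower than the full-scale one. It also speaks directly only to the four added criteria, and any impression that both raters take from the same video remains. Separate OPTION ratings by other raters would avoid the rater sharing within the full-scale comparison, but would need extra rating work.
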